## 2. Materials and Methods

The protocol of the present study has been developed, as outlined in the “Standard Protocol Items: Recommendations for Interventional Trials” (SPIRIT) guidelines [93] (Figure 1).

The study will be conducted in accordance with the Declaration of Helsinki. It has been approved by the Ethics Committee (Comitato Etico territoriale Lombardia 6, Italy; protocol number: 037883/24) of the Principal Investigator (IRCCS Istituto Centro San Giovanni di Dio Fatebenefratelli, Brescia). All patients must give their written informed consent before participating in the study. This study was registered in the clinicaltrials.gov database (identifier: NCT06657274) on 23 October 2024.

### 2.1. Trial Design

This multicentric study is a single-blinded, randomized, controlled pilot study (RCT) involving 60 subjects with CNDs (MCI, SCCs, and PD) recruited from IRCCS Istituto Centro San Giovanni di Dio, Fatebenefratelli, Brescia, IRCCS Fondazione Don Carlo Gnocchi—ONLUS, Milan, Italy and IRCCS Centro Neurolesi “Bonino Pulejo”, Messina, Italy.

After recruitment, the subjects will be randomized into one of two parallel groups: (i) the tele@cognitive group, which will receive home-based cognitive telerehabilitation (tele@cognitive treatment); (ii) the Active Control Group (ACG), which will receive home-based unstructured cognitive stimulation. All participants will undergo a clinical, functional, neurocognitive, and quality of life assessment at the baseline (T0), post-treatment (5 weeks, T1), and at the 3-month (T2) follow-up. Neurophysiological markers (TMS) and biomolecular data will be collected at T0 and T1. The trial work plan is shown in Figure 2.

### 2.2. Randomization and Blinding

The assigned group will be obtained by stratified randomization (1:1 ratio), according to clinical condition, age, and his/her performance in the Montreal Cognitive Assessment (MoCA) test [94,95,96]. Stratified randomization will be achieved by generating a separate block for each combination of covariates, and participants will be assigned to the appropriate block of covariates by a researcher blinded to the study’s aims. Details of the allocated group will be given on cards contained in sequentially numbered, opaque, and sealed envelopes. A blinded researcher will conduct the evaluations.

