### 2.3. Sample Size

In the RCT, patients will be assigned to either receive tele@cognitive protocol or a home-based unstructured cognitive stimulation (ACG). The sample size of the present study was estimated on the basis of a previous work on people within the Alzheimer’s Disease continuum [3] and it was computed on a primary outcome variable (an increase in MoCA score). Applying a two-tailed independent samples *t*-test (alpha = 0.05, beta = 0.80) and considering the effect size (d = 0.784) between two types of intervention (tele@cognitive vs. ACG), we obtained a minimum sample size of 60 subjects (30 per group), taking into account the drop-out rate.

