### 2.7. Data Collection

Demographic characteristics and cognitive reserve, evaluated with the Cognitive Reserve Index—questionnaire (CRI-q [116]), will be collected at the baseline evaluation (T0). The same trained neuropsychologist (blinded to patient treatment allocations) will assess primary and secondary outcome measures for a single patient in all visits (T0, T1, and T2). Neurophysiological and biomolecular data will be collected only at the baseline (T0) and at post-treatment (at 5 weeks, T1). A subjective assessment of the digital system’s usability will be performed at T1 using the System Usability Scale (SUS) [117], a 10-item attitude Likert scale. Best practices and standards will be adopted for the collection, storage, and treatment of the data. Clinical, functional, neurocognitive, and quality of life assessment data will be collected by clinicians and stored in a specific dataset. Data will be pseudo-anonymized so that they will not be linkable to the identities of the subjects. Neurophysiological data will be organized according to Brain Imaging Data Structure (BIDS) for non-invasive brain stimulation studies and safely stored in a dataset. Biological samples collected at T0 and T1 will be stored at −80 °C until the analyses. Biomolecular data will be safely stored in a dataset. Informed consent will be obtained from patients for the storage of all data. In more detail, the data collection in terms of data collected and tools will include:

[AIM1] Clinical, functional, neurocognitive, and quality of life data recorded at T0 (baseline), T1 (post-treatment, at 5 weeks), and T2 (3-month follow-up visit).

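### Allocation is stratified on every combination of condition, age and MoCA but not on centre, so in a three-centre trial of 60 the arms can be avoidably unbalanced within centres

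*Protocol article*

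**What the plan says.** Section 2.2 (Randomization and Blinding) of the protocol article specifies "stratified randomization (1:1 ratio), according to clinical condition, age, and his/her performance in the Montreal Cognitive Assessment (MoCA) test". It carries this out by a full cross of the factors: "Stratified randomization will be achieved by generating a separate block for each combination of covariates". Allocations are held in "sequentially numbered, opaque, and sealed envelopes"; the section does not say whether one set serves all sites or each site has its own.

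Section 2.1 (Trial Design) puts 60 patients with one of three conditions (MCI, SCCs, PD) into the trial and names three recruiting institutes. Section 2.3 (Sample Size) states the target: "we obtained a minimum sample size of 60 subjects (30 per group), taking into account the drop-out rate".

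Centre is not among the factors in section 2.2, and section 2.8 (Statistical Analysis) does not mention it. Section 2.7 adds: "The same trained neuropsychologist (blinded to patient treatment allocations) will assess primary and secondary outcome measures for a single patient in all visits".

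**The concern.** Two features pull against each other. Crossing three factors in full uses up the small sample on many thin strata, while the one structural factor that a multicentre trial always has is left to chance.

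Centre could plausibly affect change over time here. A clinician prescribes a personalised digital programme in one arm, a therapist hands out the booklet and diary in the other (section 2.5), and the recruiting units supply the tablets. If one site prescribes or supports differently, or recruits patients who change differently, and its patients fall unevenly between arms, part of the site effect appears as a treatment effect in an unadjusted comparison.

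**Working it through.** **Inputs.** From the article: 60 patients, 1:1, three conditions, three centres, factors condition, age and MoCA, d = 0.784, two-sided alpha 0.05. Assumed because not stated: 2 or 3 levels each for age and MoCA, permuted blocks of 2 or 4, equal case mix, and equal centres independent of condition.

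**The plan's own target.** A two-sided t-test with d = 0.784 and 80% power needs 27 per arm, 54 in all. With an assumed 10% drop-out, 54 / 0.9 = 60, so the stated 60 is reproduced.

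**Number of strata.**
- Fewest possible: 3 × 2 × 2 = 12, or 60 / 12 = 5 patients each.
- Three levels each for age and MoCA: 3 × 3 × 3 = 27, or 60 / 27 = 2.2 each.
- Lists held per site: 12 × 3 = 36 cells (1.7 patients each) to 27 × 3 = 81 cells (0.7 each).

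**Simulation.** At least 3,000 trials per setting; Monte Carlo error is about 2 percentage points at most. A difference of 6 overall means 33 v 27; in a centre of 20 it means 13 v 7.

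| Scheme | Strata | Block | Mean overall difference | Overall ≥ 6 | Some centre ≥ 6 |
|---|---|---|---|---|---|
| Simple randomisation | – | – | 6.1–6.2 | 51% | 52–53% |
| As written, shared lists | 12 | 2 | 1.9 | 3% | 31% |
| | 12 | 4 | 2.4 | 12% | 35% |
| | 27 | 2 | 2.8 | 17% | 36–38% |
| | 27 | 4 | 3.9 | 31% | 41% |
| As written, per-site lists | 36 | 2 | 3.2 | 23% | 6% |
| | 36 | 4 | 4.3 | 36% | 22% |
| | 81 | 2 | 4.5 | 37% | 24% |
| | 81 | 4 | 5.4 | 45% | 40% |
| Condition × centre | 9 | 2 | 1.6 | 1% | about 0% |
| | 9 | 4 | 2.1 | 6% | about 0% |
| Minimisation (0.8 coin) on condition, centre, age, MoCA | – | – | 1.1–1.3 | below 1% | about 1% |

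**What a 13 v 7 centre does.** With 30 per arm, that centre supplies 13/30 of one arm and 7/30 of the other. If its mean change differs from the other centres by δ, the unadjusted treatment contrast shifts by (13/30 − 7/30) × δ = 0.2δ. For assumed δ of 0.25, 0.5 and 1 SD the shift is 0.05, 0.10 and 0.20 SD, or 6%, 13% and 26% of the planned 0.784.

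**Power.** At d = 0.784, power is 84.8% at 30:30, 84.4% at 33:27 and 83.3% at 36:24. Overall imbalance costs little.

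**The case against.** The case against is substantial, and much of it stands.

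- A reader might infer that most blocks never fill and that the balance is largely lost. The documents do not support this. With 12 shared strata, about 27 of 33 opened blocks fill at block size 2 and 10.5 of 19.5 at size 4, and the overall difference is far below simple randomisation. Counting strata that end on an open block does not discriminate either: 9 of 12 (75%) as written with blocks of 4, and 6.7 of 9 (about 75%) under condition × centre. Section 2.2 also uses the word block in the sense of stratum, so permuted blocks are themselves an assumption.
- A reader might add the two harms together. They belong to alternative readings: shared lists leave centre unprotected, while per-site lists protect it better at the expense of overall balance.
- Outcomes are changes from baseline and one neuropsychologist follows each patient, so stable rater or equipment offsets largely cancel. Nothing in the article says that TMS equipment or sample handling differ by site. Centre must affect the change itself to matter.
- Chance imbalance after valid randomisation does not inflate type I error.
- Cut-points, block size and envelope handling are details that an article may leave to the full protocol; their absence is no finding. If centres recruit mainly different conditions, stratifying on condition partly balances centre.

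What is left is the explicit list of factors. It omits centre, and neither way of holding the envelopes makes that choice efficient across the settings examined.

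**Conclusion.** The point holds in a limited form. The factor list crosses three variables in full in 60 patients and omits centre. With shared lists, overall balance is acceptable at the minimum of 12 strata, but centre is left closer to chance than it need be (31% to 41% against about 53% under simple randomisation). With per-site lists, centre protection ranges from good (6%) to poor (40%), and overall balance worsens to a mean difference of 3.2 to 5.4.

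The consequence is avoidable centre imbalance and possible confounding of site effects on change through prescribing, therapist support or case mix. It is not a material loss of power and not a threat to type I error. All sizes rest on the assumed levels, block sizes and equal mix. That sites differ in change is an inference, not something the article states.

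**What to change.** For patients not yet randomised, allocate by central minimisation with a random element on condition, centre, age and MoCA, starting from the tallies of those already allocated. In simulation this gives a mean overall difference of about 1.2, a centre difference of 6 or more in about 1% of trials, and age balance no worse than now. For all patients, include centre together with condition, age and baseline MoCA in the between-group models; section 2.8 already allows ANCOVA.

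Cost: a central allocation tool in place of envelopes, a short amendment, and two degrees of freedom for centre.

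If envelopes must stay, use condition × centre strata (9 lists, fewer than the present minimum of 12) with age and MoCA as covariates. The price is looser age and MoCA balance: the mean difference per level rises by roughly 1.5 patients with blocks of 4. Adding centre to the existing full cross is not a remedy, because it produces the 36 or more cells shown above.

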### 2.3. Sample Size

In the RCT, patients will be assigned to either receive tele@cognitive protocol or a home-based unstructured cognitive stimulation (ACG). The sample size of the present study was estimated on the basis of a previous work on people within the Alzheimer’s Disease continuum [3] and it was computed on a primary outcome variable (an increase in MoCA score). Applying a two-tailed independent samples *t*-test (alpha = 0.05, beta = 0.80) and considering the effect size (d = 0.784) between two types of intervention (tele@cognitive vs. ACG), we obtained a minimum sample size of 60 subjects (30 per group), taking into account the drop-out rate.

### 2.4. Participants

According to the sample size calculation, the EARLY-COGN^3 trial has a target enrollment of 60 subjects with CNDs (MCI, SCCs, and PD).

#### Inclusion and Exclusion Criteria

Formal criteria-based diagnosis of MCI, SCCs, and PD will be applied.

Patients will include both male and female subjects affected by CNDs: MCI, SCCs and PD.

Inclusion criteria will include: (1) age eligible for the study: 18 ≤ age ≤ 85; (2) agreement to participate by signing the informed consent form; (3) diagnosis of PD (Hoehn & Yahr < 3 [97]), MCI (with Cognitive Dementia Rating Scale - CDR ≤ 0.5 [98] and Mini Mental State Examination - MMSE raw score ≥ 24 [99,100,101]), or SCCs; (4) native Italian speakers; (5) MoCA-corrected score ≥ 17.36 [95]; (6) education ≥ 5 years; (7) availability of a caregiver/study partner able to support the participant; (8) absence of marked hearing/visual impairment; (9) no rehabilitation program in place at the time of enrollment or in the last 3 months before enrollment; (10) stable drug treatment (last 3 months) with L-Dopa or dopamine agonists (PD group) and acetylcholinesterase (MCI group), if any.

Key exclusion criteria will include: (1) the presence of any medical or psychiatric illness that could interfere with completing assessments; (2) the presence of any medical or psychiatric illness that could make the administration of TMS unsafe.

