#### 2.6.2. Secondary Outcome Measures

The secondary outcome measures for this study will be the change from the baseline (T0) to post-treatment (T1) and 3-month follow-up visit (T2) in:Quality of life as assessed by EQ-5D-3L. EQ-5D-3L [104] is a measure of health status consisting of five dimensions (mobility, self-care, usual activities, pain/discomfort, and anxiety/depression). Each dimension has three response levels (no problems, some problems, unable to/extreme problems). In addition, the questionnaire includes a visual analog scale that records the patient’s perception of his or her overall health (score range min = 0, max = 100, higher score = better outcome).Non-motor experiences of daily living as assessed by MDS-UPDRS scale, part I. MDS-UPDRS scale [105], part I (only for the PD group) is a measure of non-motor experiences of daily living consisting of a total of 13 questions (score range min = 0, max = 52, higher score = worse outcome).Motor abilities as assessed by MDS-UPDRS scale, part III. MDS-UPDRS scale [105], part III (only for the PD group) is a measure of motor abilities consisting of a total of 18 questions with 33 individual items. Each item has a 0–4 rating, where 0 = normal, 1 = slight, 2 = mild, 3 = moderate, and 4 = severe (score range min = 0, max = 132, higher score = worse outcome).Depressive symptoms as assessed by Hamilton Depression Rating Scale (HDRS). HDRS [106] is a measure of severity of the depressive symptoms consisting of a total of 21 items (score range min = 0, max = 64, higher score = worse outcome).Anxiety symptoms as assessed by State-Trait Anxiety Inventory (STAI-Y). The STAI-Y [107] consists of two 20-item scales providing separate measures of state and trait anxiety (S-Anxiety and T-Anxiety). Each scale has a score range from a minimum of 20 to a maximum of 80, with a higher score on the scale indicating a worse outcome.Behavior and personality as assessed by Neuropsychiatric Inventory (NPI). NPI [108] is used for assessing various neuropsychiatric symptoms. The inventory consists of 12 core domains, each reflecting specific neuropsychiatric symptoms. Each symptom is rated for both frequency and severity (score range min = 0, max = 144, higher score = worse outcome).Memory complaints as assessed by Everyday Memory Questionnaire (EMQ). EMQ [109] is a 20-item questionnaire that evaluate the frequency and impact of memory problems in daily life (score range min = 20, max = 180, higher score = worse outcome).Non-verbal abstract reasoning as assessed by Raven’s Colored Progressive Matrices (CPM). CPM [110] is a measure of non-verbal abstract reasoning (score range min = 0, max = 36, higher score = better outcome).Attentional abilities as assessed by Trial Making Test (TMT). TMT (Part-A and Part-B) [111] is a measure of attentional abilities, visuo-conceptual and visual–motor tracking. TMT-Part A involves visual scanning, number recognition, number sequencing, and motor speed. TMT-Part B assesses mental flexibility in managing more than one stimulus at a time and in shifting the course of an ongoing activity. High execution times indicate poor performance (score range min = n/a, max = no limits).Executive abilities as assessed by Stroop Test. Stroop Test [112] is a measure of executive abilities, including visual attention, selective attention, cognitive flexibility, and inhibitory control of behavior. Two scores are calculated with consideration of the number of errors and the time taken to complete all parts. High execution times and high numbers of errors indicate poor performance.Constructional praxia as assessed by Rey–Osterrieth Complex Figure-Copy (ROCF). ROCF [113] is a measure of constructional praxia (score range min = 0, max = 36, higher score = better outcome).Fluency abilities as assessed by Verbal Fluency (semantic and phonemic). Verbal Fluency (semantic and phonemic) [114] is a measure of verbal and semantic fluency abilities, executive functions abilities, lexical store size, lexicon access, and lexical organization (score range min = 0, max = no limits, higher score = better outcome).Nonverbal long-term memory as assessed by ROCF-Recall. ROCF-Recall [113] is a measure of nonverbal long-term memory (score range min = 0, max = 36, higher score = better outcome).

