
#### 2.6.3. Surrogate Outcome Measures

The surrogate outcome measures will be the change from the baseline (T0) to post-treatment (T1) in:Neurofilament light chain (NF-L) and Tau levels.Aß1-40, Aß1-42, p-tau-181, p-tau-231, and alpha-synuclein levels.Glial Fibrillary Acidic Protein (GFAP), chemokines, and sTREM2 levels.Neurogranin and Brain-Derived Neurotrophic Factor (BDNF) levels.Concentration and size of plasma Extracellular Vescicles (EVs).Resting Motor Threshold (rMT). rMT reflects membrane excitability of corticospinal neurons. Lower values indicate increased excitability.Motor Evoked Potentials (MEPs). MEPs are muscle twitches resulting from complex descending corticospinal volleys occurring after TMS pulses. MEP amplitude and latency reflect the integrity of the corticospinal tract and corticospinal excitability.Short-interval intracortical inhibition (SICI). TMS-SICI reflects inhibitory interneuronal circuits acting via GABA A receptors [115].Short-latency afferent inhibition (SAI). TMS-SAI reflects cholinergic transmission [116].

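### The drug-stability criterion is narrower than the cholinergic and GABA-A markers measured in every participant; this exposes the within-arm and predictor analyses but does not bias the randomised comparison

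*Protocol article*

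**What the plan says.** All from the protocol article.

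- **Eligibility (2.4, Inclusion and Exclusion Criteria).** Three diagnoses are enrolled: "Patients will include both male and female subjects affected by CNDs: MCI, SCCs and PD". Criterion (10) requires "stable drug treatment (last 3 months) with L-Dopa or dopamine agonists (PD group) and acetylcholinesterase (MCI group), if any". The two exclusions are based on illness and introduced as key ones: "Key exclusion criteria will include: (1) the presence of any medical or psychiatric illness that could interfere with completing assessments", and illness that makes TMS unsafe. Neither concerns drugs.
- **Markers (2.6.3).** "TMS-SAI reflects cholinergic transmission", and "TMS-SICI reflects inhibitory interneuronal circuits acting via GABA A receptors".
- **Timing (2.1; details in 2.7).** "Neurophysiological markers (TMS) and biomolecular data will be collected at T0 and T1", with T1 at 5 weeks. TMS is not restricted to any diagnosis.
- **Allocation (2.2).** "The assigned group will be obtained by stratified randomization (1:1 ratio), according to clinical condition, age, and his/her performance in the Montreal Cognitive Assessment" test. Medication is not a stratum.
- **Analysis (2.8).** Between-group comparisons are planned (t-tests, ANCOVA or non-parametric tests). So are paired t or Wilcoxon tests within each arm. These are said to assess whether the intervention works over time, and they cover the collected multimodal parameters.
- **Aim 3 (Introduction).** Predictors of treatment outcome are sought among those who received tele@cognitive, 30 people as planned.

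**The concern.** The criterion treats cholinergic drug stability as important enough to require in MCI. The same cholinergic marker is measured in PD and SCCs, where no such requirement is stated. For the GABA-A marker no group has a rule. As printed, a PD participant who began a cholinesterase inhibitor shortly before T0 is eligible. So is a participant in any group who has just begun a drug acting on GABA-A receptors.

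A drug still taking effect between T0 and T1 would act over the same 5 weeks as the rehabilitation. An analysis that looks only at change inside one arm cannot separate the two. At stake are the Aim 2 statement that the treated arm develops marker changes, and the Aim 3 labels of who responded.

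**Working it through.** **1. The plan's own figure.** Inputs from 2.3: d = 0.784, two-sided alpha 0.05, and 0.80 (printed as beta) read as power. The two-sample t calculation gives 26.53, so 27 per arm. With an assumed 10% dropout (no rate is given), 27/0.90 = 30 per arm, or 60 in total. The stated size is reproduced and this point does not affect it. Power at 30 per arm without dropout is 0.848.

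**2. Criterion against markers.**

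| Group | Stability rule names | Cholinergic marker (SAI) | GABA-A marker (SICI) |
|---|---|---|---|
| PD | L-Dopa or dopamine agonists | measured, no matching rule | measured, no matching rule |
| MCI | acetylcholinesterase (inhibitors meant) | measured, rule covers these but not anticholinergics | measured, no matching rule |
| SCCs | nothing | measured, no matching rule | measured, no matching rule |

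**3. What a recent drug change does to the tests.** The documents give no prevalence or effect, so both are assumed. A proportion p of patients (5–20%) has a drug still taking effect, and each is shifted by s SD of the change (0.3–0.8), all in the same direction. There is no true treatment effect, and n = 30 per arm.

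- Spurious mean change within an arm: p × s.
- SD of the change: v = √(1 + p(1 − p)s²).
- Paired test: noncentral t on 29 df with noncentrality p × s × √30 / v.
- Between arms: expected difference p × s − p × s = 0; 95% chance range ±1.96 × s × √(2p(1 − p)/30).
- Between-arm power: d falls to 0.784/v.

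Worked for p = 0.20, s = 0.8: p × s = 0.16; v = √(1 + 0.16 × 0.64) = √1.1024 = 1.050; noncentrality = 0.16 × 5.477/1.050 = 0.83; rejection rate 0.127. Between arms: ±1.96 × 0.8 × √(0.32/30) = ±0.162 SD; d = 0.784/1.050 = 0.747; power 0.812.

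| p, s | Within-arm shift (SD) | Paired-test false positives | Between-arm chance range (SD) | Added variance | Power, 30 per arm |
|---|---|---|---|---|---|
| 0.05, 0.3 | 0.015 | 0.051 | ±0.033 | 0.4% | 0.846 |
| 0.10, 0.5 | 0.050 | 0.058 | ±0.076 | 2.2% | 0.840 |
| 0.20, 0.8 | 0.160 | 0.127 | ±0.162 | 10.2% | 0.812 |

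A simulation of 20,000 trials agrees. Between-arm type I error was 0.047 (p = 0.10, s = 0.5) and 0.050 (p = 0.20, s = 0.8). The within-arm rates were 0.059 and 0.128.

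**The case against.** **Randomisation.** Allocation is 1:1, stratified by condition, against an active control, and the Introduction says Aim 2 may show differences between the groups. Drugs started before randomisation are then balanced in expectation. This stands. A reader might infer that recent drug changes would bias the tele@cognitive versus ACG comparison, but the design does not support that. Type I error stays near 0.05 and the loss of power is small. The exception would be drug changes after randomisation that differ by arm.

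**Worst-case imbalance.** One could imagine 3 to 5 affected patients, each shifted by 1 SD, all in one arm. That moves its mean by 3/30 = 0.10 to 5/30 = 0.17 SD. Under simple 30:30 allocation this has probability 2 × C(30,3)/C(60,3) = 24% for three and 2 × C(30,5)/C(60,5) = 5% for five. It also needs every drug to act in the same direction. Nor can such a shift in SAI or SICI be scaled against d = 0.784, which was set for MoCA only.

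**Scope of the rule.** It would be wrong to say that the criterion covers one class per diagnosis or ignores cholinergic drugs. PD has two drug types named, MCI's cholinergic drugs are covered, and SCCs has none.

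**Condensed article.** The exclusions are labelled as key ones, and a fuller rule on concomitant drugs may exist in the full protocol. So the absence of such a rule is not the point. The point is that a numbered and specifically worded criterion is selective and contains a wrong term. If a fuller rule exists, this text misreports it.

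**Pharmacology.** The article says what SAI and SICI reflect, but not how far any drug moves them in 5 weeks. This also stands, and it is why the sizes above are given as assumed ranges.

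**Conclusion.** The point holds in limited form. Criterion (10) does not match the markers in 2.6.3: there is no GABA-A-related rule in any group, no cholinergic rule outside MCI, nothing at all for SCCs, and an enzyme named in place of its inhibitors. For the randomised comparison the consequence is modest: zero expected bias, 0.4–10% more variance, and power of 0.846–0.812 instead of 0.848. The real exposure lies where randomisation does not help. In the paired tests read as effectiveness, the false-positive rate is 0.051–0.13 instead of 0.05. In the predictor models of the tele@cognitive arm, drug-driven change could be labelled response; that effect was not quantified. All sizes rest on the assumed 5–20% prevalence and 0.3–0.8 SD shift in a common direction. Shifts in opposite directions would partly cancel. The correction is worth making, but it does not threaten the primary between-arm test.

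**What to change.** 1. Reconcile criterion (10) with 2.6.3, so that the existing 3-month stability requirement applies in all three groups to drugs acting on the systems the trial measures. Which drugs belong on that list is for the sponsor to decide.
2. Correct the enzyme term to its inhibitors.
3. Unless the full protocol already does so, record drug changes between T0 and T1 and give a sensitivity analysis of SAI and SICI that accounts for them.
4. In 2.8, rest the treatment-effect claim on the between-arm comparison and present the paired tests as descriptive.

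The cost is one reworded criterion, one field on the case report form, one extra analysis and a few candidates deferred until stable. It is best done before enrolment, because drug changes not recorded at the time are hard to recover later.
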